### Objectives

The protocol mainly aims to compare the cardiovascular effects and the anaesthetic efficacy of intra-osseous computerised anaesthesia (ICA) versus inferior alveolar nerve block anaesthesia (IANB) in acute irreversible pulpitis of mandibular molars. The primary objective will be the evaluation of the time taken for the cardiovascular parameters to return to their initial values before administration of ICA compared to IANB in a mandibular molar presented with irreversible pulpitis. Secondary objectives will be the efficacy of the QuickSleeper™ system compared to IANB when (i) comparing patient pain, (ii) comparing postoperative outcomes, and (iii) investigating factors associated with the time to recovery of cardiovascular parameters between the 2 anaesthetic techniques. The use of blood pressure and cardiovascular measurements can be considered an asset and additional safety in the management of local anaesthesia through the early detection of signs of potential AEs. The main risk associated with local anaesthetics is a hypersensitivity or toxicity reaction, which is considered to be low leading to a very favourable benefit/risk balance.

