### Sequence generation

Each patient, regardless of the study group allocated, will receive 1.8 mL of 4% articaine 1:100 000 for 2 min. The evaluated intervention consists of the administration of intraosseous anaesthesia using the QuickSleeper™ (DHT, Cholet, France) system, according to the manufacturer’s recommendations, in the “ICA” group. A plastic syringe with a cartridge of 4% articaine 1:100,000 epinephrine will be used in the “IANB” group. The emergency treatment will be a pulpotomy. The tooth will be isolated with a rubber dam and all carious tissue and pulpal parenchyma will be removed. Pulpal bleeding will be controlled using a 2.5% sodium hypochlorite and the site will be covered with calcium hydroxide and a temporary filling. At the end of the intervention, all patients, regardless of the randomisation group, will be given two types of antalgics (paracetamol 1 g or paracetamol 600mg/codeine 50 mg) according to preoperative pain declaration (VAS) and recommended to take them only if they experience pain, according to the good clinical recommendations.

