### Determination of sample size

The sample size calculation was based on the noninferiority hypothesis in a pilot study that there will be an expected mean difference of 1 min 30 s between the two anaesthetic techniques with regard to the time taken for the values to return to the initial ones. According to the reported results from the few studies available, the proportion of patients having successful anaesthesia and better pain control in the reference group (intraosseous anaesthesia) would be 93%. The noninferiority margin was defined as 20%. The significance was set at 1.7% for the 3 main criteria (heart rate, systolic and diastolic blood pressure) and 5% for the secondary criteria. Thus, using a bilateral test with an epiR package 0.98-87 (Biostatgv), 72 patients (36 patients per arm) will be included in the study.

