### Statistical analysis

The analysis will be based on intention-to-treat (ITT) using the “missing=failure” strategy. A robustness analysis, supported by the per-protocol approach, will be carried out if the patients present with protocol deviations (error of randomisation). Qualitative variables will be described by the percentages and numbers of each modality. Quantitative variables will be described by means and standard deviations. Confidence intervals at 95% will be presented.

A paper case report form (CRF) will be created for each patient inclusion for data collection and will be based on the establishment of a clinical database. All information required by the protocol must be provided in the CRF, necessary for statistical analyses.

To assess the primary endpoint (time to return to baseline heart rate and blood pressure), the mean values will be estimated by the Kaplan-Meier method (survival curves) and compared using Log-Rank tests. To assess the secondary endpoint (time to baseline O_2_ and change in measurements over time), the 2 arms will be compared in the same way as the heart rate and blood pressure parameters. Univariate and multivariate Cox models will be used to investigate the factors associated with the time to the baseline of cardiopulmonary constants. The difference in pain between D0 and D+3 will be compared between the 2 groups a Student’s *t*-test or a Wilcoxon test. Data for the analysis are collected from the first questionnaire (French version of Corah’s dental anxiety scale), the three phases of cardiopulmonary monitoring, the VAS assessment, and the postoperative questionnaire given to the patient at the end of the procedure. The information recorded on the postoperative questionnaire will be collected by a telephone call 3 days after the procedure. All the data collected will be typed and inserted into an Excel spreadsheet for data entry in a secure computer network of Nantes University Hospital. The investigative team, mainly the investigators as well as the study technicians involved in this study protocol will have access to the data collected.

In regard to the post-trial care, the patients will either continue their dental care with their appointed dentist, or in the case where they do not have one, they will be following appointments at the Nantes University Hospital.

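### The pain comparison named in the article (raw change from D0 to D+3) is not the anaesthetic success it defines, and it uses the baseline VAS inefficiently

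*Protocol article*

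**What the plan says.** Efficacy is part of the stated aim. The Objectives section of the protocol article sets out to "compare the cardiovascular effects and the anaesthetic efficacy of intra-osseous computerised anaesthesia (ICA) versus inferior alveolar nerve block anaesthesia (IANB"). Under Outcomes, efficacy is a secondary outcome with a two-part definition: a VAS of 0, and the pulpotomy completed. The pain times given with it are preoperative D0 and D+1 to D+3.

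The sample size paragraph relies on the same idea. It states that the proportion with "successful anaesthesia and better pain control in the reference group (intraosseous anaesthesia) would be 93"%, and gives a non-inferiority margin of 20% without naming its scale.

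Statistical analysis then assigns methods endpoint by endpoint: Kaplan-Meier and log-rank for heart rate and blood pressure, the same for oxygen, and Cox models for associated factors. For pain it says: "The difference in pain between D0 and D+3 will be compared between the 2 groups", using a Student's t-test or a Wilcoxon test. No covariate is named. For categorical data the text is descriptive: "Qualitative variables will be described by the percentages and numbers of each modality". The general rule is "The analysis will be based on intention-to-treat (ITT) using the “missing=failure” strategy".

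Both arms have the same procedure ("The emergency treatment will be a pulpotomy") and the same analgesic rule. Analgesics are given "according to preoperative pain declaration (VAS) and recommended to take them only if they experience pain".

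**The concern.** There are two separate problems.

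**Wrong quantity for efficacy.** The title and aim promise a comparison of anaesthetic efficacy, which the article defines as a binary outcome tied to treatment. The pain test it names is a continuous change that starts before anaesthesia and ends three days later. A finding of no difference on that test could be misread as equal anaesthetic efficacy, although success during the pulpotomy does not enter it.

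**Inefficient use of baseline.** D0 VAS is already collected. Subtracting it from D+3 VAS fixes its weight at 1, whatever the correlation between the two. When that correlation is modest, subtraction adds noise. With 36 patients per arm the loss matters.

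**Working it through.** **1. The plan's own figure: 72 patients (36 per arm).** It cannot be rebuilt from the stated inputs alone, because no power is given and the 1 min 30 s difference has no SD. As an assumption, read the 93% and the 20% as a non-inferiority test of success, with 93% in both arms and a 20-point margin:

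n per arm = (z₁₋α + z_power)² × 2 × 0.93 × 0.07 / 0.20²

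- One-sided 2.5%, 90% power: (1.960 + 1.282)² × 0.1302 / 0.04 = 34.2, so 35 per arm (70).
- One-sided 5%, 95% power: (1.645 + 1.645)² × 0.1302 / 0.04 = 35.2, so 36 per arm (72).
- At the stated 1.7%, no total is 72. Two-sided gives 68, 78 or 88 at 80%, 85% or 90% power. One-sided gives 58, 66 or 76.

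So 72 is compatible with a test of success, but the article does not establish that this was its basis. At 36 per arm, SE = √(0.1302/36) = 0.0601. Power at one-sided 2.5% is Φ(0.20/0.0601 − 1.960) = Φ(1.366) = 91.4%. On this reading, a comparison of success is feasible at the planned size.

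**2. The sections side by side.**

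| Section | Quantity | Time span |
|---|---|---|
| Outcomes | VAS 0 and pulpotomy completed (binary) | tied to treatment; VAS time not clearly stated |
| Determination of sample size | 93% success (binary) | not stated |
| Statistical analysis | change in pain (continuous) | preoperative D0 to D+3 |

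The third row is not an analysis of the first two.

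**3. Change score against ANCOVA.** Let s² be the common variance of D0 and D+3 VAS (assumed equal) and ρ their correlation. The article gives neither.

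- Var(change) = 2s²(1 − ρ)
- Var(ANCOVA) = s²(1 − ρ²)
- Ratio ANCOVA/change = (1 − ρ²) / [2(1 − ρ)] = (1 + ρ)/2

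The power columns use 36 per arm, two-sided 5%, and a true difference of 0.66 SD. That is the difference D+3 VAS alone would detect with 80% power: (1.960 + 0.842) × √(2/36) = 0.66.

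| Assumed ρ | Var(change)/s² | Var(ANCOVA)/s² | Ratio | 72 on change score worth, by ANCOVA | Power, change | Power, ANCOVA |
|---|---|---|---|---|---|---|
| 0.2 | 1.60 | 0.96 | 0.60 | 72 × 0.60 = 43 | 60% | 82% |
| 0.5 | 1.00 | 0.75 | 0.75 | 72 × 0.75 = 54 | 80% | 90% |
| 0.7 | 0.60 | 0.51 | 0.85 | 72 × 0.85 = 61 | 95% | 98% |

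Below ρ = 0.5, Var(change) exceeds s², so the change score is less precise than D+3 VAS with no baseline at all.

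If the variances differ, let k be the D0 SD divided by the D+3 SD. The ratio is then (1 − ρ²)/(1 + k² − 2ρk). The denominator exceeds the numerator by (k − ρ)², so ANCOVA is never the less precise of the two, but the size of the gain changes.

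**The case against.** The strongest defence is that this is a condensed article. Efficacy is a secondary outcome, and its test may sit in the full protocol or analysis plan, neither of which is shown. The article sets a 5% level for secondary criteria, promises 95% confidence intervals, and has a missing-as-failure rule that suits a binary outcome. The abstract lists efficacy and pain perception separately, and Statistical analysis calls the D0 to D+3 test a comparison of pain, not of efficacy. All of this stands, and it rules out several stronger readings:

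- **That success is never compared.** The article is silent on such a test, which is not evidence that none is planned.
- **That no VAS is taken during the pulpotomy.** The schedule of assessments (Table 1) is not shown, so this cannot be judged.
- **That the D+3 test measures only the pulpotomy and analgesics.** That may describe the change within an arm. Both arms share the procedure and the analgesic rule, so the between-arm difference is a valid contrast of postoperative pain, which the Objectives also list.
- **That the baseline VAS is wasted.** The change score uses it with weight 1 and is unbiased under randomisation. The loss is in precision, and at ρ = 0.7 it is small.
- **That the article's figures imply a 37-point gap in success (93% against 56%).** This pairs the best figure for each technique. The Background gives 42 to 93% for intraosseous pain control and 44 to 81% IANB failure, so 19 to 56% success. The gap could lie anywhere from 42 − 56 = −14 to 93 − 19 = +74 points.
- **That the 20% margin belongs to success.** Its scale is not stated, and its paragraph opens with recovery time.

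The choice of ANCOVA might also be left to an analysis plan. Here, though, the article is not silent: it fixes a different, less efficient method.

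**Conclusion.** The point holds in two limited parts. First, the article defines efficacy as a success proportion and cites that proportion when sizing the trial, yet the only pain comparison it names is a different quantity, one that cannot show anaesthetic success. This is a mismatch within the article and needs reconciling whatever an analysis plan adds. Second, the named test is valid but inefficient. Its variance could be cut to 0.60, 0.75 or 0.85 of its value at correlations of 0.2, 0.5 or 0.7, using data already collected. Those ratios rest on equal D0 and D+3 variances and on assumed correlations.

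The primary cardiovascular endpoint is unaffected. The correction is worth making because the title and aim claim efficacy.

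**What to change.** 1. Analyse D+3 VAS by ANCOVA with D0 VAS as covariate, using a rank-based or robust version if the scores are skewed. Label the result postoperative pain, not anaesthetic efficacy.
2. Report anaesthetic success exactly as defined under Outcomes, using the VAS already collected, and state when that VAS was taken. Present the between-arm risk difference with a score-based 95% confidence interval.
3. Before applying the 20% margin to success, reconcile Outcomes with Determination of sample size. The latter gives the margin no scale and calls intraosseous anaesthesia the reference group, while Outcomes calls IANB the reference technique. Until that is settled, give the interval without a non-inferiority claim.

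The cost is analysis-plan wording and a few lines of code. No new data are needed. New data collection would not be realistic in any case: inclusion was due to end on 1 July 2022 and the article appeared on 5 December 2022. For the same reason, an extra VAS entry is not proposed. Completion of the pulpotomy alone should not stand in for success, because it would drop half of the stated definition.

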### Protocol violations

All protocol violations occurring after randomisation will be listed in the clinical report form (CRF) and tabulated by the subject. The final assignment of participants to the per-protocol analysis will be decided at a blinded protocol review meeting before locking the database.

### Adverse events

Considering the low risks and constraints of this study, no adverse event related to the trial is expected. In addition to the measurements of blood pressure and heart rate variations, which are the objectives of the present protocol, the suspected AEs related to the administration technique or anaesthesia will be traced in the CRF and analysed according to the study schedule by internal monitoring. They will not be notified to the sponsor, even if they are serious. Any adverse event is linked to a failure of anaesthesia.

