**Fig. 1 Fig1:**
[figure not shown]
Flowchart of a trial evaluating the noninferiority of ICA QuickSleeper™ system versus IANB anaesthesia for the pain management in the emergency care of irreversible pulpitis in mandibular molars at the Nantes University Hospital

The investigator in charge of the emergency room will proceed to randomisation (see below) using a secure computer program called Ennov Clinical and will conduct the emergency endodontic treatment. The patient will then be contacted by a research assistant 72h following the intervention by telephone to assess the pain perception and if any secondary effects of the anaesthesia occurred, as depicted in Table 1. Part or all of the study may be discontinued permanently or temporarily by the decision of the ANSM, the CPP, and the Study Sponsor (Nantes University Hospital).

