Furthermore, this technique has considerable expected benefits (patient comfort, rapidity of action, reproducibility). In addition, there is less risk of technical failures, such as a blocked or broken needle and the ability to retrieve the needle. The QuickSleeper™ system is also able to administer the anaesthetic solution at varying speeds, in the context of a para-apical or an intraligamentary injection with the same device regardless of the location, density, and resiliency of the soft tissues at the injection site.

Adverse effects of intraosseous anaesthesia are associated with an elevated heart rate (tachycardia, malaise). The main causes of an elevated heart rate are related to the patient's perception, fear, and anxiety, exacerbated by the symptoms of irreversible pulpitis or by the amount of vasoconstrictor used. Because this elevation is transient, it does not pose a serious cardiovascular risk, rendering its effect negligible. In patients whose medical condition suggests caution in administering epinephrine, mepivacaine may be an acceptable alternative [24]. The main objective of this trial will be to conclude that the time required for the cardiorespiratory parameters to return their initial values will be similar to the two anaesthetic techniques used. This study should provide better data about potential risk with ICA technique such as the QuickSleeper™ system in healthy or cardiovascular-risk patients.

This new approach in dentistry would increase the number of successful pulpal anaesthesia in emergency endodontic treatments by avoiding IANB failures and alleviating compliance of patients.

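### Adverse events enter the CRF only if suspected to be related, in a trial where the treating investigator knows the arm, so the between-arm count is open to attribution bias

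*Protocol article*

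**What the plan says.** The rule stands in the Adverse events section of the protocol article: "the suspected AEs related to the administration technique or anaesthesia will be traced in the CRF". These events are then "analysed according to the study schedule by internal monitoring". The same section opens with the expectation that "no adverse event related to the trial is expected".

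On who knows the arm, the text under Study timelines says: "The investigator in charge of the emergency room will proceed to randomisation". The same person "will conduct the emergency endodontic treatment". Under Randomisation, the software returns the allocated group to the investigators who enter the patient. Only the patient is described as blinded (Interventions; Allocation concealment mechanism).

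Post-operative effects have their own route. The patient receives a questionnaire at the end of the procedure, and its content is collected by telephone three days later (Statistical analysis). A research assistant makes the call, which is described as assessing pain and "if any secondary effects of the anaesthesia occurred" (Study timelines).

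**The concern.** When relatedness is a field on a recorded event, a reader can look at all events, at related events, or at both, and a doubtful attribution can be reviewed. When relatedness decides whether the event is written down at all, the attribution is hidden in the count. If it is made with knowledge of the arm, two arms with the same true event rate can show different recorded rates, or a true difference can be masked.

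The article gives separate grounds for attribution in each arm. In the Discussion, "Adverse effects of intraosseous anaesthesia are associated with an elevated heart rate (tachycardia, malaise"), but the main causes given for a raised heart rate are the patient's fear and anxiety, made worse by the pulpitis or by the amount of vasoconstrictor. For the nerve block, the Discussion names biting and burning of lip and tongue, nerve injury and haematoma. A malaise in the chair could reasonably be put down to the injection or to the patient's state, and the choice may differ by arm.

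At stake is the safety description. The Discussion says the trial should give better data on the potential risk of the intraosseous technique, and with 36 patients per arm a few events attributed differently can change the picture.

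**Working it through.** The plan states no adverse event rate, so there is no figure to reproduce. The check sets the sections side by side; a short calculation then shows what the mechanism could do.

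1. **Entry rule.** Adverse events section: suspected relation to technique or anaesthesia comes first, then the CRF. This is a stated rule, not a detail left out of a condensed article.
2. **Knowledge of the arm.** Study timelines and Randomisation: the investigator randomises, receives the group and treats. The treating investigator therefore knows the arm.
3. **Who judges relatedness.** No section says. No blinded assessor is named.
4. **Later checks.** Internal monitoring analyses what has already been traced in the CRF, so it comes after the filter. The sponsor is no second route either: "They will not be notified to the sponsor, even if they are serious". (Whether that is acceptable is a separate matter.) No analysis plan can restore an event that was not recorded.
5. **What escapes the filter.** Heart rate, systolic and diastolic pressure and oxygen saturation are monitored throughout the intervention in every patient (Interventions), and the Adverse events section treats adverse events as additional to the blood pressure and heart rate measurements. Tachycardia during treatment is therefore captured whatever its supposed cause. What remains exposed is chiefly subjective events at the visit, such as malaise.
6. **The 72 h route.** It runs from patient to questionnaire to research assistant. The treating investigator's attribution is not a stated step. The call's purpose is still worded by cause, as effects of the anaesthesia.

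**Illustration.** Input from the plan: 36 patients per arm (Determination of sample size). Assumptions, not in the documents: a true event rate *r*, equal in both arms, and probabilities *q*₁ and *q*₂ that an event is suspected to be related in each arm.

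Expected recorded events in an arm = 36 × *r* × *q*. False difference = *r* × (*q*₁ − *q*₂).

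| *r* | *q*₁ v *q*₂ | Recorded events per 36 | False difference |
|---|---|---|---|
| 10% | 90% v 70% | 3.24 v 2.52 | 2 points |
| 10% | 90% v 50% | 3.24 v 1.80 | 4 points |
| 20% | 90% v 70% | 6.48 v 5.04 | 4 points |
| 20% | 90% v 50% | 6.48 v 3.60 | 8 points |
| 30% | 90% v 70% | 9.72 v 7.56 | 6 points |
| 30% | 90% v 50% | 9.72 v 5.40 | 12 points |

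With *q*₁ = *q*₂ the difference is zero in every row. Exchanging *q*₁ and *q*₂ reverses the sign. The table shows a mechanism; it does not estimate a bias in this trial.

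**The case against.** A reader might infer that the operator who gave the injection decides whether an event is related. The documents do not say so. They say that the treating investigator knows the arm, and they do not name who decides on relatedness.

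A reader might also infer that the comparison of post-operative effects, a secondary outcome, rests on a biased count. The documents do not support that. Those data come from a questionnaire given to a patient described as blinded and collected by a research assistant, and no section links the CRF adverse event list to that outcome. The description of the call is a one-line summary. The questionnaire and the call wording are not shown and may already be neutral, so it cannot be said that patients must attribute an event before reporting it.

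The claim that cardiovascular effects would be undercounted fails for the measured parameters, which are taken in everyone. The statement that no related event is expected is a risk statement in an article, not an instruction to staff.

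Condensation of the full protocol is a fair reply on who assesses relatedness and how the CRF is laid out. It does not answer the entry rule, which the article states outright.

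Timing also counts against the fix. Trial status gives recruitment from March 2019 and final inclusion on 1 July 2022, and the article is dated 5 December 2022. A changed CRF cannot recover events that were not recorded. This limits what the fix can achieve; it does not make the rule sound.

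**Conclusion.** The concern holds as a risk. A causality filter at entry, an investigator who knows the arm and no named blinded assessor together leave the between-arm adverse event count open to attribution bias, mainly for subjective events during the visit. Size and direction are unknown, because the documents give neither event rates nor attribution probabilities; the 2 to 12 points above depend wholly on the assumed values. The point assumes that attribution can differ by arm, which the different effects named for each technique make plausible but do not show. It does not touch the monitored cardiovascular parameters, and it does not show that the comparison of post-operative effects is biased.

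A smaller inconsistency stands beside it: the expectation of no related event does not fit the effects that the Discussion names for both techniques. This is a cheap improvement worth making, not a threat to the primary comparison.

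**What to change.** In the Adverse events section, replace the entry rule: record every untoward event from injection to the 72 h call, in both arms, whatever its suspected cause, with relatedness as a separate CRF field. State who completes that field and whether that person knows the arm. Compare arms on all events, and give related events in a secondary table.

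At the 72 h call, ask about events in cause-neutral terms and identically in both arms, and state whether the research assistant is blinded. Reconcile the expectation of no related event with the effects named in the Discussion.

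The cost is one CRF field and a neutral wording in a call that already takes place; the downside is some unrelated events in the listing. For patients already followed up under the present rule, the report should say that the count covers suspected related events only and that relatedness was not assessed by a named blinded person, if that was so.

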## Abstract

**Background:**

Irreversible pulpitis is a highly painful inflammatory condition of the dental pulp. The recommended care is the removal of the coronal pulp (pulpotomy) for emergency treatment in multi-rooted teeth. However, achieving adequate analgesia in the case of mandibular molars presents many difficulties according to the dental literature. Intraosseous computerised anaesthesia (ICA), in particular, the QuickSleeper™ system, has already been demonstrated to be clinically efficient, but ICA is known to increase the heart rate reversibly in a manner that depends on the speed of injection. Therefore, accelerated heart rate was examined as a potential adverse effect of this injection. This trial aims to compare the cardiovascular effects and the anaesthetic efficacy of ICA versus inferior alveolar nerve block anaesthesia (IANB) in acute irreversible pulpitis of mandibular molars.

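### The adverse-event section excludes notifying the sponsor of serious suspected related events, although the sponsor has a stopping role, and ties every adverse event to failed anaesthesia, contrary to the article's own account of the risks

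*Protocol article*

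**What the plan says.** The Adverse events section of the protocol article makes four statements that matter here.

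- Expectation: given the low risks, "no adverse event related to the trial is expected".
- Recording and review: alongside the blood pressure and heart rate measurements, "the suspected AEs related to the administration technique or anaesthesia will be traced in the CRF"; internal monitoring then reviews them on the study's timetable.
- Notification, referring to those same events: "They will not be notified to the sponsor, even if they are serious".
- Attribution: "Any adverse event is linked to a failure of anaesthesia".

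Under Study timelines, in the text that follows Fig. 1, the article says: "Part or all of the study may be discontinued permanently or temporarily by the decision of the ANSM, the CPP, and the Study Sponsor". It identifies the sponsor as Nantes University Hospital.

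**The concern.** Two rules look wrong as written. Both are positive statements, so a fuller protocol or an analysis plan would have to contradict them to repair them.

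The first is the exclusion of the sponsor. A body with a say in stopping the trial needs to hear of serious events suspected to come from the technique or the drug. Under the stated rule it is not told of them. The only review named follows the study schedule, and no faster route is given for a serious event.

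The second is the attribution sentence. It settles the cause, or the classification, of every adverse event before any has been seen. The article presents cardiovascular monitoring as a means of catching adverse events early and says the trial should give better data on the risks of the intraosseous technique. An adverse-event summary built on a preset attribution would serve that aim poorly. The events the article names also differ by technique: systemic effects for intraosseous injection, soft-tissue and nerve effects for the block. An attribution error could therefore bear unequally on the two arms.

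**Working it through.** No arithmetic applies, since the point does not depend on alpha, power, margin or sample size. The check is to set the sections of the protocol article side by side.

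**Step 1: notification against stopping role**

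- Study timelines: the ANSM, the CPP and the sponsor are named as deciding on discontinuation.
- Adverse events: suspected related events are not notified to the sponsor, serious ones included.
- Result: the sponsor has a stopping role but is denied notice of the related serious events most relevant to it. The article says nothing either way about notifying the other two bodies.

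**Step 2: the attribution sentence against the risks named elsewhere**

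| Section | Event described | Source given or implied | Needs failed anaesthesia? |
|---|---|---|---|
| Abstract, Background | "accelerated heart rate was examined as a potential adverse effect of this injection" | The injection | No |
| Background | Faster heart rate | Rapid diffusion in the diploë plus vasoconstrictor | No |
| Objectives | Hypersensitivity or toxicity reaction, called the main risk | The anaesthetic drug | No |
| Discussion | Biting or burning of lip and tongue after a block | Prolonged numbness | No; it arises because tissue is numb |
| Discussion | Mandibular nerve injury, haematoma | The block technique | No |
| Discussion | Tachycardia, malaise | Intraosseous anaesthesia | No |

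Every event in the table can occur when the anaesthesia works.

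**Step 3: the attribution sentence against the efficacy definition**

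The Outcomes section defines efficacy as a pain score of 0 with the pulpotomy completed. Adverse events do not enter. Take a patient with a score of 0, a completed pulpotomy and tachycardia with malaise. Under Outcomes this patient is a success. Under Adverse events the event is tied to a failure.

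The word for the tie can be read in two ways:

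- *Caused by failure.* This conflicts with the sources in the table.
- *Counted as failure.* This conflicts with the Outcomes definition.

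Neither reading agrees with the rest of the article.

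**Step 4: the expectation sentence**

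The article expects no related event, yet the Objectives name a main risk and the Discussion states: "Adverse effects of intraosseous anaesthesia are associated with an elevated heart rate (tachycardia, malaise". The Objectives also call the risk low, and the Discussion calls the heart-rate rise transient and negligible. The wording is therefore loose and needs aligning, but this is the weakest of the conflicts.

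**The case against.** Several counter-arguments are sound and set the limits of the point.

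- A reader might infer that serious events are concealed from the sponsor. The text does not support that. Events go into the CRF, internal monitoring reviews them, and a telephone call at 72 hours asks about secondary effects. The sponsor is also the hospital where the trial runs. What is stated is the absence of notification.
- The notification sentence covers suspected related events only. How other serious events are handled is not stated, so nothing can be concluded about them.
- The sponsor is not the only body with a stopping role. The conflict concerns the sponsor alone.
- A reader might infer that the trial's cardiovascular comparison would be misclassified. It would not. Heart rate and blood pressure are monitored throughout the intervention, form the primary outcome and are compared by Kaplan-Meier and log-rank methods. The adverse-event section says events are traced in addition to those measurements.
- A reader might infer that an adverse event would be coded as an efficacy failure. That is one reading of an ambiguous sentence, and no coding rule of that kind appears.
- A confidence limit for zero events in an arm of 36 would hold whoever is notified, so it does not measure this defect.
- Expecting no event in 72 healthy (ASA 1) patients can coexist with naming a low risk.
- Whether regulation permits non-notification for research of this kind cannot be judged from the article.
- Final inclusion was set for 1 July 2022 and the article appeared on 5 December 2022, so a new notification rule may come too late to act during recruitment.

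These arguments narrow the point without removing it. None explains why a body with a stopping role should be excluded from notice of serious related events, and none reconciles the attribution sentence with the efficacy definition or the named risks.

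**Conclusion.** The point holds in limited form. The article contradicts itself in two places: between the sponsor's stopping role and the rule against notifying it of serious suspected related events, and between the blanket tie to failed anaesthesia and both the efficacy definition and the article's own account of where adverse events come from. The expectation sentence needs rewording to match.

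The size is qualitative. The defect touches the reporting and attribution of adverse events in all 72 planned patients. It does not touch the primary outcome, the sample size or the error rates. It should be corrected for the sake of patient safety and a usable adverse-event summary.

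The conclusion assumes that the notification sentence refers to the suspected related events in the sentence before it, and that the article reproduces the full protocol's rule faithfully. It does not assume that any regulation has been breached.

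**What to change.** 1. Reconcile the Adverse events and Study timelines sections by requiring that serious suspected related events be notified to the sponsor.
2. Delete the sentence that ties every adverse event to failed anaesthesia.
3. Record a suspected cause for each event in the CRF (drug, injection technique or dental procedure), and tabulate adverse events by arm whether or not anaesthesia succeeded.
4. Reword the statement that no related event is expected so that it agrees with the risks named in the Objectives and Discussion.
5. If inclusions have already ended, have the sponsor review serious events already in the CRFs, assign suspected causes from those records, and apply the tabulation at analysis.

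The cost is a reporting sentence, one causality field and a short table specification for 72 patients: a small administrative load. The changes themselves call for no new measurement and leave the primary analysis as it is.
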